### Trial design {12}

Using a two-arm clinical design, participants will be randomized in a 1:1 allocation to be placed in either the 12-week LightBEAM program or the waitlist control. After the 12-week LightBEAM program has been completed by the intervention condition, participants in the waitlist control group will have one month to complete the “re-baselining questionnaires and online orientation prior to gaining access to the LightBEAM intervention. Participants in the intervention condition will complete post-questionnaires at the same time that the waitlist control completes re-baselining questionnaires. Longitudinal self-report questionnaires will be administered digitally at three timepoints: pre-intervention, post-intervention, and at six months follow-up.

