##### Re-baselining questionnaires

All participants who are randomized to the waitlist control condition will complete an additional set of questionnaires prior to gaining access to the online LightBEAM content. Participants in the waitlist control condition will have a one-month period to complete these questionnaires.

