11	Boundary setting to make space for everything else	Memory making with your kiddo
12	Staying well and moving forward	Recipe for wellness

#### Aim 2

All eligible participants must present with at least one elevated symptom of concern across parental anxiety (GAD-7), depression (PHQ-9), anger (PROMIS) and/or parenting stress (PSI). Based on which metric(s) participants screen in as being elevated, an individualized composite primary score will be created whereby we examine whether there is a statistically significant change in elevated symptoms of concern across assessment time points. To examine the efficacy of the LightBEAM program in improving parental outcomes, a multi-level model with random intercepts will be utilized to assess the effect of treatment over time based on conditions. An intent to treat approach will be followed such that all randomized participants are included in analysis, regardless of completion.

Specifically, we will examine pre-to-post-to follow up program changes in primary and secondary outcomes. Such analysis will allow us to examine the efficacy of the LightBEAM program compared to other community resources. Program engagement metrics (e.g., number of videos watched, see Table 4) will also be included as moderators to probe whether participant changes are due to program engagement. This dosage analysis will be an exploratory analysis.

**Table 4 Tab4:** Aim 1 feasibility and acceptability metrics

	Indicator	Benchmark	Rational
Recruitment Rate	Number of parents recruited per month	Approx. 50 parents	We want at least 50 parents in the forum to ensure maximum engagement
Retention Rate	% of parents with follow up data	> 70% of parents with follow up data	Average retention rate amongst previous MOOI’s is 70%
Forum Use	# of posts and comments made on the forum	> 50% of users engage at least once in the forum (i.e., through posting, responding or interacting with a message)	This is an exploratory outcome. Based on previous work that showed 57% engagement in the BEAM forum
Videos watched	% of videos watched at least 50% of the way through	Participation in > 50% of the LightBEAM Content	Utilizing same benchmark (e.g., 50%) used in previous BEAM pilot studies [13]
Symptom tracking	# of weekly surveys completed	Participation in > 50% of symptom tracking exercises	Based on benchmark used in previous BEAM pilot studies

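### The efficacy analysis runs to a six-month follow-up at which the waitlist already has LightBEAM, and the plan does not fix the one clean contrast (intervention post versus waitlist re-baselining) as the efficacy test

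*Protocol article*

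**What the plan says.** Objectives sets Aim 2 as efficacy against a waitlist control. Trial design adds that "participants will be randomized in a 1:1 allocation to be placed in either the 12-week LightBEAM program or the waitlist control".

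Once the intervention arm has finished its 12 weeks, the waitlist has one month to complete its re-baselining "questionnaires and online orientation prior to gaining access to the LightBEAM intervention". The same section makes the two assessments concurrent: "Participants in the intervention condition will complete post-questionnaires at the same time that the waitlist control completes re-baselining questionnaires". It then describes questionnaires as "administered digitally at three timepoints: pre-intervention, post-intervention, and at six months follow-up". The section on re-baselining says: "All participants who are randomized to the waitlist control condition will complete an additional set of questionnaires", before the content is opened to them. Table 1 gives Re-Baselining and Post-Intervention separate columns.

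Statistical methods, Aim 2, plans a random-intercept multilevel model of treatment over time by condition, and continues: "Specifically, we will examine pre-to-post-to follow up program changes in primary and secondary outcomes". The next sentence reads: "Such analysis will allow us to examine the efficacy of the LightBEAM program compared to other community resources". The section on the analysis population keeps every participant in the arm to which they were randomised. Time coding, a primary time point and the handling of the waitlist's later data are not given.

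**The concern.** The randomised comparison of treated with untreated participants ends when the waitlist gains access. The efficacy model, as described, goes on to a follow-up after that point and keeps the waitlist as the control arm. No section confines the between-arm test to the earlier window or marks follow-up as uncontrolled.

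The analysis text also never mentions re-baselining, although that is the waitlist's only untreated assessment after the programme period. It does not say which record serves as the waitlist's post value.

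The same wording therefore permits analyses that keep, halve or erase a real effect. The choice carries further: Aim 3 adds moderators to the same model, the interim analysis addresses all three aims and may prompt a rethink of the design, and the data analysts are not blinded. The comparator is also described in terms that match neither Objectives nor Trial design.

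**Working it through.** There is no plan figure to reproduce. The target of 200–500 in total (100–250 per arm at 1:1) rests on feasibility, with no alpha, power, effect size or SD.

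**Step 1. Who has been treated at each assessment** (Trial design, Re-baselining questionnaires, Table 1)

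| Assessment | LightBEAM arm | Waitlist arm | Contrast |
|---|---|---|---|
| Pre-intervention | no access | no access | baseline |
| Intervention post / waitlist re-baselining (concurrent) | programme completed | no access | treated v untreated |
| Waitlist's own post-intervention | – | programme completed | no untreated group |
| Six-month follow-up | treated | has access | no untreated control |

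The origin of the six months is not stated. Counted from baseline, the waitlist gains access at about month 3 to 4 (12 weeks plus up to one month), so it has had roughly two to three months of access. Counted from programme end, it has had longer. It has access on every reading, but how far it has caught up is unknown.

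**Step 2. Expected arm differences**

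Let d be the true benefit at post in SD units, assumed to persist in the LightBEAM arm. Let c be the fraction of it that the waitlist has gained by follow-up. The arm differences at pre, post and follow-up are (0, d, (1−c)d).

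- Categorical post contrast: d.
- Average of post and follow-up: d(1 − c/2).
- Follow-up only: (1−c)d.
- Linear slope, times 0, 1, 2: (1−c)d/2.
- Linear slope, times 0, 3, 9 months: mean 4, deviations −4, −1, 5, sum of squares 42, so [−d + 5(1−c)d]/42.

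Full catch-up (c = 1): the average is d/2, follow-up is 0, the slope is 0 at equal spacing and −d/42 = −0.024d per month at 0/3/9. With d = 0.40, the average is 0.20 and the 0/3/9 slope is −0.0095 SD per month.

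Half catch-up (c = 0.5): the average is 0.75d, follow-up is 0.5d, and the 0/3/9 slope is 1.5d/42 = 0.036d, against 4d/42 = 0.095d with no crossover.

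**Step 3. Power**

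Assumptions, none from the document: d = 0.3, SD 1, within-person correlation ρ = 0.5, two-sided alpha 0.05, complete data. Under a random-intercept covariance, a contrast with weights w summing to zero has variance (1−ρ)Σw² × 2/n between arms. That is 2/n for post change, 1.5/n for the average and 1/(42n) for the 0/3/9 slope. The rejection probability is Φ(z − 1.96) + Φ(−z − 1.96), with z the absolute difference over its standard error.

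At 100 per arm with full catch-up:

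- post: z = 0.3/√0.02 = 2.12, power 56%;
- average: z = 0.15/√0.015 = 1.22, power 23%;
- slope: z = (0.3/42)/√(1/4200) = 0.46, rejection 7.5%, with the estimate in the wrong direction.

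Rejection probability at 100 / 250 per arm:

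| Test | Full catch-up | Half catch-up | No crossover |
|---|---|---|---|
| Post contrast, categorical time | 56% / 92% | 56% / 92% | 56% / 92% |
| 2-df condition-by-time | 58% / 94% | 46% / 86% | 58% / 94% |
| Average of post and follow-up | 23% / 49% | 45% / 83% | 69% / 97% |
| Linear slope, 0/3/9 months | 7.5% / 11% | 10.7% / 19.5% | 46% / 83% |
| Follow-up only | 5% / 5% | 18.5% / 39% | 56% / 92% |

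With equally spaced times and full catch-up, the slope test rejects at 5%. If only 70% are retained, the Table 4 benchmark (70 or 175 per arm), the post contrast has 43% or 80% power.

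**Step 4. Which waitlist record is the post value**

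If re-baselining is used, the post contrast is treated versus untreated and the figures above apply. If the waitlist's own Post-Intervention record were used, both arms would have had the programme. The expected difference would be 0 if the waitlist gains the same benefit.

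**The case against.** A reader might infer that every contrast after baseline is treated versus treated, and that a real effect is bound to be averaged away. The document does not support that. Trial design pairs the intervention arm's post assessment with the waitlist's re-baselining, which precedes access, so the natural reading of the post contrast is clean. Aim 2 does not name re-baselining, but it does not exclude it either. Using the waitlist's own Post-Intervention record would be a misreading that the text leaves open; it is not something the plan states. With categorical time, the post contrast keeps the full effect even if later waitlist data stay in the model. Time coding is the kind of detail an article may leave to a fuller document. Full catch-up, equal pooling and a nine-month follow-up are assumptions, and the reversed slope depends on the last of these. All of this stands, and it limits the claim about size.

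The comparator phrase also has a plausible reading. Concomitant mental health care is allowed and measured by the service utilization questionnaire, so waitlist participants may be using community services. That makes it a wording correction; it does not show that the model fails.

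What the objection does not answer is that the plan uses follow-up by original arm for efficacy when the control arm has access under every time coding, and that it never sets apart the one contrast that is controlled.

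**Conclusion.** The point holds in a limited form. The six-month between-arm contrast has no untreated control, and the plan does not fix intervention post versus waitlist re-baselining as the efficacy test. This follows from the protocol's own text and needs no assumption.

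The loss of effect is conditional. Under full waitlist catch-up it is none for a categorical post contrast, half for a pooled effect, and all for a linear slope or follow-up-only test. Under half catch-up the pooled effect keeps 75% and the follow-up contrast 50%. The power figures rest further on the assumed 0.3 SD effect and correlation of 0.5. A certain loss of effect is not shown. The description of three timepoints and of the comparator are lesser inconsistencies that should be corrected at the same time.

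**What to change.** - Name intervention post versus the concurrent waitlist re-baselining as the primary efficacy contrast, with time categorical and adjustment for baseline.
- Keep waitlist data after re-baselining out of that contrast, either by excluding them or by giving them their own time level. Either is acceptable if stated in advance.
- Report six-month follow-up as within-arm maintenance or as early versus delayed access, and not as controlled efficacy.
- State in Trial design that the waitlist has an additional re-baselining assessment.
- In Aim 2, name the waitlist control as the comparator in place of community resources.

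The cost is analysis wording only, because the schedule already collects the data needed. The price is that the six-month result can no longer be claimed as controlled efficacy. Since the analysts are unblinded, the contrast should be fixed before efficacy results by arm are seen, the interim analysis included.

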### Objectives {10}

There are three main aims of the proposed study. The first aim is to assess the feasibility and acceptability of the LightBEAM program. Metrics to examine feasibility will include recruitment and retention rates, participant satisfaction, and an exploration of unmet needs. As a way to explore feasibility, we will utilize qualitative focus groups to examine ways in which the program can be improved to better support Canadian families. Aim two is to examine the efficacy of LightBEAM at improving family outcomes when compared to a waitlist control condition. Primary outcomes for parents include mental health, distress, and parenting quality. Secondary outcomes for children include child well-being and socioemotional development. Aim three is to identify groups associated with the greatest program engagement and improvements. This will promote equity and be used to inform future programming.

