#### Tracking concomitant care during trials {15d}

Participants will be allowed to receive concomitant care for mental health problems.

Use of additional interventions will be assessed through a service utilization questionnaire and subsequently controlled for in analyses to account for potential confounding effects.

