## Methods: assignment of intervention {21a-b, 22, 24a-c}

### Allocation

Using the built-in randomization functionality within REDCap, participants will be randomly allocated to either LightBEAM or the waitlist control condition.

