### Ancillary and post-trial care {34}

All participants will receive a list of crisis resources upon completion of the eligibility screener. A provincial-specific list of community resources and counselling services will be provided to participants via email if they are not eligible to participate in the LightBEAM study.

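### The Aim 2 analysis is described as a comparison with community resources, but the design identifies only a comparison with a waitlist, and only up to the post-intervention assessment

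*Protocol article*

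**What the plan says.** The Aim 2 text first defines the model: "a multi-level model with random intercepts will be utilized to assess the effect of treatment over time based on conditions". It says that changes from pre-intervention to post-intervention to follow-up will be examined, and then states what this delivers: "Such analysis will allow us to examine the efficacy of the LightBEAM program compared to other community resources".

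The sections that define the comparison name something else:

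- Objectives {10}: "Aim two is to examine the efficacy of LightBEAM at improving family outcomes when compared to a waitlist control condition".
- Trial design {12}: "participants will be randomized in a 1:1 allocation to be placed in either the 12-week LightBEAM program or the waitlist control".
- Allocation: "participants will be randomly allocated to either LightBEAM or the waitlist control condition".

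The section on concomitant care {15d} lets participants receive other mental health care, with no distinction by arm. It says that use of additional interventions will be measured and "subsequently controlled for in analyses to account for potential confounding effects". On community resources themselves, Ancillary and post-trial care {34} says: "A provincial-specific list of community resources and counselling services will be provided to participants via email if they are not eligible".

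**The concern.** The sentence stands in the statistical methods for the efficacy aim and tells the reader which question the analysis answers. The comparator it names is not an arm of the trial.

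Better than waiting and better than existing services are different claims. The Dissemination section says that findings will go to agencies, community partners and policy makers, for whom the difference bears on whether LightBEAM adds to local services or could stand in for them. If the sentence is carried into a report, a positive result could be read as evidence against existing services that the trial never collected. That is a risk created by the wording. The protocol does not announce such a claim.

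**Working it through.** The plan gives no figure on this point, and no power or error calculation applies. The check is whether the design contains the contrast that the sentence names.

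**1. Which arms exist.** Trial design and Allocation give two: LightBEAM and waitlist, 1:1. Participants allocated to community resources: 0 at either end of the planned 200 to 500 (Sample size {19}). A larger sample does not change this.

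**2. What the model estimates.** The treatment effect over time is estimated by condition, and the conditions are those two arms. Up to the post-intervention assessment the contrast is:

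- LightBEAM plus any concomitant care, against
- waitlist plus any concomitant care.

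**3. Where community services enter.** They can enter in three ways, and none makes them a comparator.

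- As permitted background care. This is open to participants in either arm and is neither assigned nor defined.
- As a covariate. Under {15d}, service use is controlled for as a potential confounder. An analysis that adjusts for service use is not a comparison with it.
- As a moderator. Aim 3 puts service-related variables into the same model. That asks whether the LightBEAM-versus-waitlist effect differs by service use, which is again not a comparison with services.

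The resource list in {34} is described for people found ineligible, who are not randomised. The crisis list goes to everyone after the screener and does not separate the arms.

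**4. Follow-up.** The waitlist arm gains access to LightBEAM after the 12 weeks and up to one month for re-baselining. Taking a month as 30 days, that is 84 + 30 = 114 days. The article does not say whether six months runs from the start or from the end of the programme. On the shorter reading, follow-up falls at about 182 days, so controls have had access for about 182 − 114 = 68 days. On the longer reading, from the end of week 12, they have had about 182 − 30 = 152 days. Both figures assume that access follows re-baselining and orientation without further delay. On either reading, follow-up compares two arms that have both been offered LightBEAM.

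**Result.** The only controlled contrast is with the waitlist, at the post-intervention/re-baselining assessment. A contrast with community resources is not identified at any time point.

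**The case against.** The strongest defence is that waitlisted caregivers may use whatever is available locally, so the waitlist amounts to usual community care and the sentence is loose wording for that. Part of this stands. Some participants, perhaps many, may use such services, and the service utilization questionnaire is scheduled at pre-intervention, re-baselining, post-intervention and follow-up (Table 1). The planned model is already LightBEAM against waitlist, so the error is one of expression and not of computation. But no section defines the waitlist as community or usual care, the same care is open to the LightBEAM arm, and the plan treats it as a confounder.

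A reader might also infer more than the documents support:

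- *That no randomised participant receives community services.* None is allocated to them. The number who use them is unknown.
- *That waitlisted participants are denied the resource list.* Section {34} says that ineligible people are sent it. It does not say that it is withheld from others.
- *That the analysis is said to show superiority or equivalence to services.* The text says only that it will examine efficacy against them. No section plans such a claim.
- *That a waitlist is the wrong control.* That is a design choice and not an error in the plan. Expectation effects under an unblinded waitlist are a general limitation and do not bear on this mismatch.

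**Conclusion.** The point holds as a misstatement of the comparator. The Aim 2 sentence attributes to the analysis a comparison that the design does not contain. The Objectives, Trial design and Allocation sections agree with one another and with the model, so the sentence is the outlier.

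In size, it changes what the trial may conclude. It changes no model, outcome, sample size or error rate. The conclusion rests on the article's own account of the two arms, on concomitant care being open to both, and on controls being offered LightBEAM before follow-up. A separate statistical analysis plan could restate the comparison correctly, but the published sentence would still need correcting. It should be corrected before results are reported.

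**What to change.** Replace the sentence with wording to this effect:

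> The analysis will estimate the efficacy of LightBEAM against a waitlist control, with concomitant care permitted in both arms, at the post-intervention/re-baselining assessment. Six-month follow-up takes place after controls have been offered LightBEAM and is not a comparison with an untreated control.

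Make no claim relative to community resources. Report the service use already being collected, by arm, as description. This is in addition to the adjustment planned under {15d} and does not replace it.

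The cost is the replacement of one sentence, a descriptive table from data already scheduled, and a narrower claim. Design, sample size and data collection stay as they are.

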### Participant identification, recruitment, and consent {20, 32a}

Participants will be recruited from across Canada using a variety of online social media posts (e.g. Instagram, Facebook), radio ads, and through local organizations (e.g., daycares, community centers etc.). Once recruited, participant informed consent will be obtained via REDCap on two separate occasions; prior to completing the eligibility screener and before becoming enrolled in the program (i.e. before completing pre-questionnaires). Participant Canadian residency will be verified through checking their IP addresses. Should we not be able to verify their residency through IP, we will require participants to upload a photo of their Canadian identification (e.g., driver’s license, passport) alongside a photo of themselves. This verification process is designed to ensure only Canadian residents are accessing the LightBEAM program. The study team has successfully used this form of identity verification across other iterations of BEAM.

During the main consent process, all eligible participants will be asked if they would like to invite a co-parent to complete the LightBEAM program alongside them. Here, we define co-parent as the child’s other parent, stepparent, or other primary caregivers (e.g., child’s grandparents, uncle, auntie, etc.). If the main parent wishes to invite a co-parent to the program, they will be asked to enter their co-parent's email address. The co-parent will then complete a main consent form. Once co-parents have consented, they will go through the same identity verification, randomization, and assessment procedures outlined below.

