### Eligibility criteria {14a}

Eligible participants must (a) identify as a primary caregiver of any gender to an 18 -to 107-month-old child (e.g., 1.5 - 8 years of age), (b) reside in Canada with access to an internet connection, (c) be aged 18 years or older, (d) be able to understand/read/speak in English, (e) report mild emotional distress across at least one of the following metrics; depression (Patient Health Questionnaire- 9 ≥ 5), anxiety (Generalized Anxiety Disorders Questionnaire ≥ 5) anger (Patient Reported Outcomes Measurement Information System Anger ≥ 14), or parenting stress symptoms (Parenting Stress Index Fourth Edition ≥ 110), and (f) have access to an electronic device. On the screener questionnaire, participants will be asked to contact the study coordinator via email if they do not have access to an electronic device as we will be able to provide a limited number of devices to those who do not have access. Although many parenting programs are open to caregivers who are parenting children under the age of six, LightBEAM includes caregivers who are parenting children up to the age of eight. Such a wide and inclusive age range was intentional to address the many behavioral challenges and delayed diagnosis that children encounter later in childhood, while also considering inclusivity and general lack of programming for parents of children who are older. Participants will be excluded if they are (a) below the age of 18 years, (b) parenting a child outside the designated age range, (c) live outside Canada, (d) have participated in previous iterations of BEAM. Co-parents will be subjected to similar inclusion and exclusion criteria as the main participant, however they will not have to report mild emotional distress. As such to be eligible, co-parents must (a) reside in Canada with access to internet connection, (b) be aged 18 years or older (c) be able to understand, read, and speak English and have access to an electronic device.

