### Participant timeline {18}

The LightBEAM program will use a rolling recruitment model whereby eligible participants will be randomized and gain access to the program on the first Monday of each month (e.g., all eligible participants who complete the screener questionnaire during the month of September will be randomized and gain access to the program on the first Monday in October). This rolling recruitment model will continue until the target sample size is reached. While participant timeline in the program will vary within this model, all participants will complete the aforementioned questionnaires in the same order regardless of program start date. Co-parents will engage in the same process described below as the main participant, with the exception that co-parents will not (a) complete the screener questionnaire or (b) complete the Child Behavioral Checklist.

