##### Pre-intervention, post-intervention and follow-up questionnaires

All eligible participants (i.e., main participants and co-parents) will be asked to complete additional questionnaires that assess other factors known to influence parental mental health such as sleep and self-compassion (i.e. Patient Reported Outcomes Measurement Information Symptom [PROMIS] Sleep Scale [40], The Self-Compassion Short Form Questionnaire [4, 28]). Aspects of the parent–child relationship, child development and family dynamic will also be assessed using a variety of questionnaires (i.e., The Parenting Scale, Irvine et al. [12], Child Behavioral Checklist [3]). Additionally the authors generated an emergency service utilization questionnaire (see Roos et al. [29]) and an adapted version of the National Survey for Children’s Mental Health [8] to assess various sociodemographic, service utilization and health factors related to child and family development. All questionnaires will be completed via REDCap. See Table 1 for a full list of study measures and subsequent timepoints.

**Table 1 Tab1:** Schedule for questionnaire administration: main participant

LightBEAM Proposed Metrics					
Questionnaire	Eligibility	Pre-Intervention	Re-Baselining	Post-Intervention	Follow-Up
Pre-Screener	X				
Patient Health Questionnaire	X	X	X	X	X
Sociodemographic		X			
Generalized Anxiety Disorders	X	X	X	X	X
Self-Compassion		X	X	X	X
PROMIS Anger	X	X	X	X	X
PROMIS Sleep		X	X	X	X
Parenting Stress Index	X	X	X	X	X
Social Support Effectiveness		X	X	X	X
CBCL		X	X	X	X
Parenting Scale		X	X	X	X
App Usage				X	
Service Utilization		X	X	X	X
Modified NMH		X	X	X	X

*PROMIS* Patient Reported Outcome Measurement Information Systems, *CBCL* Child Behavioral Check List, *NMH* National Survey for Children’s Mental Health, *App Usage* Author Generated App usage questionnaire

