Acceptability	Self-reported implementation metrics	Score > 4 considered strong implementation	Based on benchmark used in previous BEAM pilot studies

The acceptability aim is assessed using an online questionnaire designed for app based mental health programs. See Appendix 2 for a full list of questions

#### Aim 3

To examine the characteristics of families who benefited most from the LightBEAM program, demographic characteristics and service-related variables will be included as moderators in the same multi-level model discussed in objective 2. Sociodemographic factors (i.e., age, marital status, number and age of children) will also be examined to determine for whom the LightBEAM program is best suited for.

On an exploratory basis, we will use regression to examine the effects of several potential moderators (e.g., child age, severity of child baseline problems, previous caregiver mental health diagnosis, household chaos, gender of caregiver) to understand how various social groups differentially experience the program.

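### Caregiver gender is tested as a moderator without separating caregiver role, so a difference between distress-selected main participants and unselected co-parents could show as a gender difference

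*Protocol article*

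**What the plan says.** Four parts of the protocol article bear on this.

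- **Who is randomised.** Under Participant identification, recruitment, and consent {20, 32a}, consenting co-parents are told that "they will go through the same identity verification, randomization, and assessment procedures outlined below". The section on pre-intervention, post-intervention and follow-up questionnaires counts them as participants: "All eligible participants (i.e., main participants and co-parents) will be asked to complete additional questionnaires".
- **Who is selected for distress.** Under Eligibility criteria {14a}, a main participant must be elevated on at least one of four scales. For co-parents the rule is waived: "however they will not have to report mild emotional distress". Participant timeline {18} adds that "co-parents will not (a) complete the screener questionnaire".
- **Who is analysed.** Under Statistical methods, Aim 2, "all randomized participants are included in analysis, regardless of completion". The section on the analysis population {27c} repeats this for all participants.
- **What is tested.** Under Aim 3, "On an exploratory basis, we will use regression to examine the effects of several potential moderators". The examples include "previous caregiver mental health diagnosis, household chaos, gender of caregiver) to understand how various social groups differentially experience the program". Role (main participant or co-parent) is not among them, and no other section names it as a covariate or restriction.

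**The concern.** Read together, these parts describe a sample that mixes caregivers selected for distress with caregivers who were not selected. Unselected caregivers may have less room to improve, so the treatment effect may differ by role. If the gender mix also differs by role, the men and women in the analysis contain different proportions of unselected caregivers, and a gender-by-arm term in a model without role picks up part of the role difference.

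Randomisation does not prevent this. It balances the arms, not the make-up of each gender group. Allowing for clustering within households would correct the standard errors but would leave the estimate biased.

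Aim 3 is intended to promote equity and to guide later programming. A result that LightBEAM helps one gender less, when the real contrast is between roles, could misdirect that work.

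**Working it through.** The article states no figure on this point, and its sample size (200 to 500) is set by feasibility without statistical inputs. There is nothing to reproduce, so the check uses assumed inputs over a range.

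**Assumed inputs (none is in the article)**

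- f = share of women among main participants: 0.5, 0.7, 0.9
- c = co-parents per main participant: 0.1, 0.3, 0.5
- q = share of co-parents whose gender is opposite to that of their main participant: 0.5, 0.8, 1.0
- Treatment effect 0.40 SD in main participants and 0.10 SD in co-parents, the same for both genders. The gap is 0.30 SD and there is no true gender moderation.
- c and q do not depend on the main participant's gender.

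**Formulas, per main participant**

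- Co-parent women: Wc = c[(1 − f)q + f(1 − q)]
- Co-parent men: Mc = c[fq + (1 − f)(1 − q)]
- Share of men who are co-parents: pM = Mc / (Mc + 1 − f)
- Share of women who are co-parents: pW = Wc / (Wc + f)
- Apparent gender difference in effect (women minus men) = 0.30 × (pM − pW)

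**Worked example (f = 0.9, c = 0.3, q = 0.8)**

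- Wc = 0.3 × (0.08 + 0.18) = 0.078
- Mc = 0.3 × (0.72 + 0.02) = 0.222
- pM = 0.222 / 0.322 = 0.69
- pW = 0.078 / 0.978 = 0.08
- Apparent difference = 0.30 × (0.689 − 0.080) = 0.183 SD

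**Results over all values of c and q**

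| Women among main participants | Apparent gender difference, gap 0.30 SD | Same, gap 0.10 SD (divide by 3) |
|---|---|---|
| 50% | 0 | 0 |
| 70% | 0.023 to 0.109 SD | 0.008 to 0.036 SD |
| 90% | 0.084 to 0.230 SD | 0.028 to 0.077 SD |

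**Effect on the test.** Ordinary least squares was simulated with 1,500 runs per setting, a two-sided 5% level, unit SD and the 0.30 SD gap. N counts main participants and co-parents together. Household clustering was not simulated.

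| N, f, c, q | Rejects, role omitted | Mean gender-by-arm term, role omitted | Rejects, role and role-by-arm added | Mean term, role added |
|---|---|---|---|---|
| 200, 0.9, 0.3, 0.8 | 10.6% | 0.197 | 5.6% | 0.009 |
| 500, 0.9, 0.3, 0.8 | 14.7% | 0.186 | 5.1% | 0.009 |
| 500, 0.9, 0.5, 1.0 | 23.6% | 0.229 | 5.1% | −0.015 |
| 500, 0.5, 0.3, 1.0 | 5.1% | −0.003 | 5.2% | −0.004 |

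The last row matters. With main participants split evenly there is no bias, even when every co-parent has the opposite gender.

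**The case against.** The strongest case on the other side has five parts.

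1. **The analysis is exploratory and the moderator list is open.** It is introduced as a set of examples, and the model and population for such regressions can be settled in an analysis plan that is not shown. This stands as a reason to rate the point low. It does not remove the point, because the article itself sets the analysed population as everyone randomised.

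2. **Co-parents may not enter every model.** Aim 2 opens by saying that all eligible participants have an elevated symptom, which conflicts with Eligibility criteria {14a}. It then builds the primary composite from screening scores, and co-parents have none. This stands for the composite, which is undefined for them. It does not cover the separate scales in the co-parent schedule, such as depression, anxiety, anger and the Parenting Scale.

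3. **Opposite gender within a couple is not enough.** A reader might infer that mixed-gender couples alone confound role with gender. The calculation shows otherwise: the gender mix must differ between roles. The article states no such imbalance. It admits main participants of any gender, and a co-parent may be a grandparent or another relative.

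4. **The effect sizes are a guess.** The 0.30 SD gap comes from no section of the article. The entry threshold is only mild distress on one of four scales, so some co-parents may meet it too. This stands, and the result shrinks in proportion.

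5. **A false gender finding is not the likely outcome.** A reader might infer that the trial would report one. Even in the worst simulated setting the test rejected in 23.6% of runs, so more than three quarters showed no significant gender difference.

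A reader might also extend the argument to previous mental health diagnosis, which is in the same list. The article gives no ground for saying that diagnoses are rarer among co-parents, so that extension is not supported.

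**Conclusion.** The point holds as a conditional and minor one. As written, co-parents are among those analysed, they enter without the distress criterion, and nothing separates role from gender in the exploratory moderator analysis. A role difference could therefore appear as a gender difference on the scales that co-parents complete.

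Its size cannot be fixed from the article. It depends on the imbalance of gender between roles, the number of co-parents and the gap in effect between roles. At the assumed gap, a strongly imbalanced sample could give a spurious difference of up to about 0.2 SD, whereas a moderate imbalance gives about half that or less. The zero result under balance assumes that c and q are the same for male and female main participants. The point says nothing against the comparison of the two arms under Aim 2.

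**What to change.** Under Statistical methods, Aim 3, state one of the following:

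- the gender moderator effect is estimated in main participants only; or
- co-parents are kept, the model includes role and role-by-arm (by time where repeated measures are modelled), and the gender term is read within role.

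Both use data already collected. Role is known from the consent route, and the sociodemographic questionnaire is in both schedules. In the simulation, the second option brought the spurious term to about 0 (−0.015 to 0.009 SD in the imbalanced settings) and the rejection rate to 5.1% to 5.6%.

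The cost is one sentence and a wider interval for the minority gender. As an illustration with N = 200, f = 0.9, c = 0.3 and q = 0.8, there are 200 / 1.3 = 154 main participants and 46 co-parents. Men number about 154 × 0.1 = 15 among main participants and 46 × 0.74 = 34 among co-parents. With unit SD and equal arms, the standard error of the effect in men is 2/√15 = 0.52 SD in main participants only, against 2/√49 = 0.29 SD with both roles pooled. The narrower interval belongs to an estimate that mixes the two roles.
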